## Abstract

**Introduction:**

Depression is associated with negative patient outcomes for chronic diseases and likely affects consistent physical non-communicable diseases (NCDs) care management in relation to clinic attendance and medication adherence. We found no published studies on the integration of depression management in physical NCD clinics in Malawi and assessing its effects on patient and service outcomes. Therefore, the aim of this study is to evaluate the effectiveness of integrating depression screening and management in physical NCD routine care on patient and service outcomes in Malawi. We will also determine the sensitivity and specificity of the Patient Health Questionnaire-9 (PHQ-9) in the detection of depression in NCD clinics.

**Methods and analysis:**

The study will have two phases. Phase I will involve the validation of the PHQ-9 screening tool for depression, using a cross-sectional study design involving 323 participants, in two specialised physical NCD clinics in one of the 28 districts of Malawi. Using a quasi-experimental study design in four districts of Malawi not involved in the phase I study, the phase II study will evaluate the effectiveness of integrating depression screening (using PHQ-9) and management (based on a specially designed toolkit). Outcomes will be measured at 3 months and 6 months among patients with comorbid diabetes (poorly controlled) and depression attending physical NCD clinics in Malawi.

**Ethics and dissemination:**

Ethical approval was obtained from the University of Malawi, College of Medicine Research and Ethics Committee (COMREC) on 31 August 2017 (reference P.07/17/2218). The findings will be disseminated through presentations at journal clubs, senior management of the Ministry of Health, national and international conferences as well as submission to peer-reviewed publications. Policy briefs will also be created.

**Trial registration number:**

PACTR201807135104799.

Strengths and limitations of this studyThe cross-sectional study design in phase I will allow us to estimate the prevalence of depression among people with diabetes.The quasi-experimental design will enable us to investigate the impact of depression in determining the outcome of diabetes.The quasi-experimental design which will be used in the second phase has a limitation that baseline differences between the clinics may lead to spurious results.

## Introduction

Physical non-communicable diseases (NCDs) and depression individually are common and significant causes of morbidity, disability and mortality in sub-Saharan Africa.^1^ NCDs account for a growing burden on the population and health systems in low-income and middle-income countries (LMICs).^2^ Similarly depression is projected to become a leading cause of disability by 2030.^3^ The World Health Survey of 2007 suggests that the prevalence of comorbidity of physical NCDs and depression is increasing; thus between 9.3% and 23.0% of people with NCDs had comorbid depression worldwide.^4^ The global prevalence of major depression in people with diabetes is 27%.^5^ The relationship between depression and physical NCDs is bidirectional. Modifiable risk factors for physical NCDs are exacerbated by poor mental health and on the other hand physical NCDs are a risk factor for mental illness.^6^ Comorbidity is associated with a range of outcomes, including poor adherence or non-adherence to medication, functional impairment, increased medical costs, poor self-care regimens, increased medical symptom burden, and increased morbidity and mortality.^7–9^ The recent international study involving 14 countries shows that people with diabetes have depressive disorder as well as significant levels of depressive symptoms. Management of depression (pharmacological treatment combined with psychotherapy) in diabetes mellitus has been shown to be effective both on depression outcomes as well as diabetes management and glycaemic control.^10 11^

Physical NCDs are common and in Malawi, it is estimated that NCDs account for at least 12% of total disability-adjusted life years.^12^ In addition, NCDs are the second leading cause of deaths in adults after AIDS.^12^ Furthermore, a 2009 nationwide STEPwise approach to Surveillance Survey showed that about 6% of the general population had diabetes mellitus.^13^

Depression commonly overlaps with physical NCDs and depression complicates NCD care. We are not aware of any studies done in Malawi that assessed the burden of depression in physical NCD care and its effect on diabetes outcomes. A recent study done in one of the 28 districts of Malawi reported that control of diabetes is poor and there was high non-adherence of NCD clients to appointments.^14^ Currently there are no published studies done in Malawi to explore factors associated with poor control of diabetes and the high rate of non-adherence to attending appointments in physical NCD clinics.

In Malawi, there are few studies looking at depression screening and treatment in general care. The prevalence of depression among outpatient attendees in primary care clinics in Malawi in 2010 and 2013 ranged between 19% to 30%.^15 16^ Despite the high prevalence of depression in general healthcare services in Malawi, the extent of comorbid depression in the context of NCDs is unclear. Using the results from general primary care clinic studies done in Malawi on detection rates for depression, it is likely that detection rates of depression in physical NCD clinics in Malawi are poor. Undiagnosed and untreated depression more likely contributes to poor control of diabetes as shown in studies done in other countries.^17–20^ Evidence from a recent international study shows that identification and treatment of mental health problems is not routine in clinical care.^20^ In Malawi, routine screening will assist in early detection of patients with comorbid depression in physical NCD clinics and facilitate treatment. To our knowledge, there are no studies done in Malawi focusing on identification and interventions for depression in physical NCD clinics. The integration of mental healthcare into other health services is one of the strategies in the National Mental Health Policy in Malawi.^21^ The results of the proposed study will help to inform on decisions whether to integrate the strategies for depression management in physical NCD clinics in Malawi.

## Aims and objectives

Our overall objective is to evaluate the effectiveness of integrating screening and depression management into physical NCD routine care on patient and service outcomes in Malawi. In this way, we will contribute to evidence on comorbidity of depression and diabetes including the effects of identifying and treating depression in patients with comorbid diabetes and depression in physical NCD care in Malawi.

Our study has four specific objectives:To determine the sensitivity and specificity of the Patient Health Questionnaire-9 (PHQ-9) in the detection of depression in NCD clinics.To estimate the prevalence of comorbidity between depression and diabetes mellitus in Malawi.To determine detection rate of depression in physical NCD clinics in Malawi.To compare patient outcomes in physical NCD clinics with and without integration of depression screening and management.

## Research questions

The main research questions in this study are:Will the validated Chichewa PHQ-9 demonstrate satisfactory sensitivity and specificity in physical NCD clinic settings in Malawi?Will integrating depression screening using a validated PHQ-9 and depression management (based on a specially designed toolkit) be more effective than usual care in identifying patients with comorbid depression and diabetes, facilitating treatment of depression in patients with comorbid depression and diabetes, and improving clinical outcomes among patients with comorbid depression and diabetes?

## Methods and analysis

The study will be conducted from December 2017 to December 2018. The study will be in two phases. Phase I will be for validation of PHQ-9 among diabetes patients. Phase II will be evaluating the effectiveness of integrating screening and depression management in patients with comorbid depression and diabetes attending physical NCD clinics. To answer the research questions, we will use a cross-sectional study design in phase I and a quasi-experimental study design in phase II.

### Patient and public involvement

Patients and or public were not involved in the design of this study; however the results will be disseminated to study participants through the clinics' diabetes support groups.

### Phase I: Validation of PHQ-9 in a physical NCD clinic setting in Malawi

#### Study design, area and physical NCD clinics

Depression varies based on cultural context as such screening tools must be adapted and validated for particular populations. PHQ-9 has not been validated in Malawi hence the study will assess validity of PHQ-9. For phase I, we will use a cross-sectional study design. The study will be conducted in Lilongwe district which is one of the 28 districts in Malawi. Malawi is divided administratively into three regions namely Northern, Central and Southern. Lilongwe is located in the central region of Malawi. It has a population of 2688 379 people^22^ with eight physical NCD clinics.

The study will be conducted in two physical NCD clinics (Area 25 Health Centre under Lilongwe District Health Office and Kamuzu Central Hospital). The Area 25 Health Centre serves a catchment population of 80 000 while the catchment population of Kamuzu Central Hospital (a tertiary health facility) is the entire central region which is 7401 068.^22^ The physical NCD clinic at Area 25 Health Centre is staffed by clinical officers and nurses who have undergone appropriate training in the diagnosis and management of key NCDs while the clinic of Kamuzu Central Hospital is also staffed by medical officers (general medical doctors) and specialists on top of clinical officers and nurses. The two sites are implementing the WHO Package of Essential NCD (WHO PEN) interventions. Figure 1 is a map of Malawi showing the central region districts.

**Figure 1 F1:**
[figure not shown]
Map of Malawi showing the central region districts and study sites.

## Sample size determination

The sample size was calculated based on the sensitivity of PHQ-9 using Buderer’s formula.^23^ We used the following parameters; anticipated sensitivity was 80%, standard normal deviation corresponding to the specified size of the critical region (z²₁₋_α/2_) is 3.84, the size of the critical region, alpha (*α),* is 0.05, z is corresponding to the level of significance and is 1.96, L is the absolute precision desired on either side of sensitivity and was set at 0.1 and prevalence for depression was 20%. The prevalence of depression of 20% is based on a recent study on patients attending a healthcare setting in Malawi.^15^ We also considered potential participants’ refusal and loss of data; consequently we put it at 5%. Taking these assumptions into consideration, the required sample size was calculated as 323.

## Recruitment and data collection

Consecutive patients attending the NCD clinic will be identified by research assistants. The research assistants will provide information about the study to the patients and seek informed written consent. Participants will be eligible for the study if they are at least 18 years of age and are attending the NCD clinics for diabetes care and are available for an interview. Participants will be excluded if they require acute medical care or are unable to speak.

The research assistants will enrol patients who consent and carry out interviews at the health facility. When patients do not consent to participate in the study, the research assistant will request permission to record sex, age, level of education and occupation of the patient.

One research assistant will administer PHQ-9 orally to ensure high and standard responses due to low literacy of the study participants. The research assistant will then calculate the screening score and let the participant be attended to by the NCD clinician. After the consultation the patient will have the Diagnostic and Statistical Manual of Mental Disorders (DSM–IV), Axis I disorders Clinical Version Structured Clinical Interview for DSM (SCID) administered by a second research assistant to elicit the psychiatric symptoms itemised in the DSM criteria for depression. The second research assistant will be masked from the PHQ-9 Score. The training, supervision and quality assurance of the research assistant doing the SCID will be done as well. A diagrammatic representation of the process is shown in figure 2.

**Figure 2 F2:**
[figure not shown]
Phase I study procedure. NCD, non-communicable disease; PHQ, Patient Health Questionnaire.

## Measurements

The aim of phase I is to validate PHQ-9 in physical NCD clinics in order for it to be used for screening of depression in NCDs in Malawi. PHQ-9 (based on DSM criteria) has been chosen for this study because it is brief, requires a short time to administer and is compatible with the Malawian health setting workload. Furthermore, the PHQ-9 can be used to establish depressive disorder diagnoses as well as depressive symptoms' severity.^24^

For screening data using PHQ-9, presence of depressive symptoms will be defined as having a total score of 5 and above on all the nine questions (PHQ-9 total score ≥5). Symptoms will be categorised using established cut-off points 5, 10 and 20 (mild, moderate and severe depressive symptoms, respectively).^25 26^ The sensitivity and specificity at the standard cut-off point will be assessed, and performance at an alternative cut-off point will also be examined to determine whether the standard cut-off point is optimal in this population

SCID for depression will be used as the gold standard to validate PHQ-9. SCID for depression has been translated into Chichewa and has been used in Malawi after undergoing a process of validation which included translation, back translation and testing.^27^

### Data management

Data will be checked for consistency and completeness by the principal investigator and double entered to SPSS V.20 by experienced data entry clerks. Then, it will be cleaned and analysed using the same V.20 of SPSS. Hard copies of the data will be stored in a locked cabinet and consent forms will be separated from the data.

### Data analysis

Data will be analysed using SPSS V.20. Descriptive statistics will be computed to describe the sociodemographic characteristics of participants and to summarise the frequencies of depression under each category in both criteria (PHQ-9 and SCID). We will assess whether refusal is associated with sociodemographic characteristics by testing the statistical significance of sociodemographic characteristics between refusers and consenters. The prevalence of diagnosed depression among patients with diabetes will be determined by computing the proportion of those with depression according to SCID; these patients will be correctly screened out by PHQ.

The sensitivity, specificity and predictive values of a PHQ-9 total score ≥5, with 95% CIs, will be calculated relative to the reference standard of a diagnosis from the depression module of SCID. A receiver operating characteristic curve (ROC curve) will be made using SPSS V.20 in order to get criterion validity of PHQ-9. Internal consistency will be determined by Cronbach’s α. In exploratory analyses we will examine the test characteristics of alternative thresholds.

### Phase II: evaluation of the effectiveness of integrating screening using validated PHQ-9 and depression management in physical NCD clinics

#### Study design and setting

In phase II of the study, we will use a quasi-experimental design employing a non-equivalent control group (prepost) design. Prospective controlled interventional trials provide a higher level of evidence for a true causality.^28^ The best choice of the controlled interventional studies is the true experimental design of which RCT is the gold standard. However a non-randomised control group trial is a reasonable choice when an RCT would be ideal but not feasible due to costs and ethics limitations and also when trying to establish the effectiveness of large-scale dissemination and implementation.^28 29^ Furthermore, literature indicates that the interventions often cannot be randomised for the following reasons: ethical considerations, an inability to randomise patients, an inability to randomise locations or settings, and a need to intervene quickly.^29^ We have therefore chosen to use a quasi-experimental design and the intervention programme will be done in two district NCD clinics while the other two districts will provide usual care. Four convenient physical NCD clinics which are implementing the WHO PEN interventions will be allocated to intervention arm (two physical NCD clinics) and control arm (two physical NCD clinics) and in each clinic. Consecutive patients who meet the study criteria will be recruited.

The phase II of the study will be conducted for a period of 9–12 months in four healthcare facilities in Mchinji district, Kasungu district, Salima district and Dedza district of the central region of Malawi (figure 1). The four districts are also implementing the WHO PEN interventions. Currently each district has one physical NCD clinic based at the district hospital. The physical NCD clinics in the four districts are staffed by clinical officers and nurses who have undergone appropriate training in the diagnosis and management of key physical NCDs. They follow similar standard guidelines in the management of physical NCDs.

#### Intervention

Clinicians at the physical NCD clinics will be trained in routine screening for depression with a validated PHQ-9.Clinicians at the physical NCD clinics will be trained on comorbidity of diabetes and depression and on coming up with individual care plans and prescribing and monitoring antidepressants.Clinicians at the physical NCD clinics will be trained on problem-solving skills using effective helping techniques for depression and on how to follow-up individual care plans.

#### Usual care

This would involve the NCD clinicians treating patients with comorbid depression and diabetes using normal practices of treating depression involving antidepressants.

## Sample size determination

The sample size was based on detecting a difference in glycated haemoglobin (HbA_1_c) at 6 months between the study arms. It was based on an analysis of covariance (ANCOVA) approach, with the outcome measurement at follow-up, and the baseline HbA_1_c considered as a covariate in the analysis. The correlation between baseline and follow-up haemoglobin values is estimated to be 0.5. A difference in HbA_1_c between arms of 0.7% is considered to be a clinically important difference (based on a previous study which found a difference of 0.56%,^30^) and data from previous research suggested that the HbA_1_c measurements had an SD of 1.8%.^30^ It is calculated that using a 5% significance level and 80% power; 78 subjects per group are required. It is estimated that there will be a 10% dropout/loss to follow-up. To allow for this, we planned to recruit 87 subjects per group, giving a total sample size for the study of 174 participants.

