### Data analysis

The primary outcome is HbA_1_c at 6 months. This will be compared between groups using ANCOVA. The haemoglobin value at baseline will be considered as a covariate in the analysis.

The HbA_1_c values at 3 months will be considered as a separate outcome, and analysed using equivalent methods to the primary outcome.

Quantitative data will be analysed statistically using SPSS V.20. Descriptive analysis will be done. The recorded qualitative data on the feasibility and acceptability of integrating depression management will be transcribed and coded using Atlas.ti. Relevant queries will be created in the database to thematically analyse the data.

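### Phase II assigns whole clinics, two per arm, so its stated 80% power and 5% error rate hold only if the between-clinic variance is zero

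*Protocol article*

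**What the plan says.** All references are to the Phase II part of the protocol article.

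- **Study design and setting.** Four conveniently chosen district clinics are split between the arms without randomisation: "the intervention programme will be done in two district NCD clinics while the other two districts will provide usual care".
- **Intervention.** The programme consists of training the clinicians of the intervention clinics. Under The primary exposure variable, exposure is defined by the type of facility where the patient is treated. All patients of a clinic are therefore in the same arm.
- **Sample size determination.** The calculation is a two-group ANCOVA on 6-month HbA1c: "It is calculated that using a 5% significance level and 80% power; 78 subjects per group are required". Its inputs are all given: "A difference in HbA_1_c between arms of 0.7% is considered to be a clinically important difference"; "HbA_1_c measurements had an SD of 1.8" percentage points; "The correlation between baseline and follow-up haemoglobin values is estimated to be 0.5"; "It is estimated that there will be a 10% dropout/loss to follow-up". The result is 87 recruited per group, 174 in total. No ICC or design effect is mentioned.
- **Data analysis.** On 6-month HbA1c: "This will be compared between groups using ANCOVA". The baseline value is the only covariate named.
- **Limitations of the study**, and the strengths and limitations box. Both warn that clinics may differ at baseline and that this may mislead. Neither mentions the standard error or the power.

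**The concern.** When whole clinics are assigned, the difference between arms contains the difference between clinics. With two clinics per arm, that component is averaged over only two units on each side, and recruiting more patients in the same clinics does not shrink it. A patient-level ANCOVA without a clinic term tests the arm effect against variation between patients only. If clinics differ in their 6-month HbA1c for any reason other than the intervention, the standard error is too small and a chance difference between districts can be declared an intervention effect. Adjusting for each patient's baseline HbA1c does not remove clinic-level variation that arises during follow-up.

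This is the test of the primary outcome, and the article intends the result to inform whether depression care is integrated into these clinics nationally.

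**Working it through.** **1. Reproduce the stated size.** Inputs from Sample size determination: difference 0.7, SD 1.8, correlation 0.5, 5%, 80%, dropout 10%. Sidedness is not stated. Two-sided is inferred because it gives 78, whereas one-sided gives 62.

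- n per group = 2 × (1.96 + 0.8416)² × 1.8² × (1 − 0.5²) / 0.7² = 77.85, so 78.
- Dropout: 78 / 0.9 = 86.7, so 87 per group and 174 recruited.

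Both figures match exactly with a design effect of 1, so no allowance for clinics is hidden in them. The power rests on 2 × 78 = 156 analysed patients; 174 is the number recruited.

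**2. Assumptions.** The article gives no ICC. I take 0.01, 0.02 and 0.05, meaning the clinic share of the variance left after baseline adjustment. I also assume that the 156 analysed patients split evenly: 156 / 4 = 39 per clinic.

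**3. Formulas.**

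- Adjusted SD = 1.8 × √0.75 = 1.559.
- Standard error for independent patients = 1.559 × √(2/78) = 0.2496.
- Design effect DE = 1 + (39 − 1) × ICC.
- True standard error = 0.2496 × √DE.
- (a) Type I error of the patient-level ANCOVA = 2 × [1 − Φ(1.96/√DE)].
- (b) Rejection rate of the same ANCOVA at a true difference of 0.7. It rejects beyond 1.96 × 0.2496 = 0.489, so the rate is about Φ[(0.7 − 0.489) / (0.2496 × √DE)].
- (c) Power of a z-test whose standard error is corrected with a known ICC = Φ[0.7 / (0.2496 × √DE) − 1.96].
- (d) Power of a clinic-level t test: non-central t on 4 − 2 = 2 degrees of freedom, critical value 4.303, non-centrality 0.7 / (0.2496 × √DE).

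**4. Results.**

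| ICC | DE | (a) ANCOVA type I error | (b) ANCOVA rejection rate at 0.7 | (c) corrected z-test power | (d) clinic-level t test power, 2 df |
|---|---|---|---|---|---|
| 0 | 1.00 | 5% | 80% | 80% | 35% |
| 0.01 | 1.38 | 9.5% | 76% | 67% | 28% |
| 0.02 | 1.76 | 14% | 74% | 56% | 24% |
| 0.05 | 2.90 | 25% | 69% | 38% | 17% |

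Worked line for ICC 0.02: √1.76 = 1.327 and the true standard error is 0.331. (a) 1.96/1.327 = 1.477, giving 14%. (b) 0.211/0.331 = 0.64, giving 74%. (c) 0.7/0.331 − 1.96 = 0.15, giving 56%.

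A simulation with 20,000 replicates per setting agrees. The ANCOVA's type I error was 9.0%, 13.6% and 25.5% for the three ICCs, and its rejection rate at 0.7 was 75.9%, 73.2% and 69.6%. The clinic-level test held 5% throughout, with power 28.0%, 23.2% and 16.5%.

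**The case against.** **The full protocol or the SAP may handle clinics.** This stands in part. A journal article may leave a clinic term to a document not shown here, so its absence from Data analysis is supporting evidence and not the fault in itself. The power statement is different: it is fixed in the article, and its inputs leave no room for a design effect. A later clinic-aware analysis could restore the 5% error rate but not the 80% power. The 2-df test reaches only 35% even if clinics do not vary.

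**The article admits that clinics may differ, and calls the design non-equivalent.** True, and to its credit. That caveat concerns bias from baseline imbalance. It does not widen the interval or lower the stated power.

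**No ICC is given, so nothing is proved.** A reader might infer that the 5% and 80% are simply false. The documents do not support that: with zero between-clinic variance, both figures hold for the patient-level ANCOVA. What they support is that the figures depend on an unstated assumption, and that even an ICC of 0.01 nearly doubles the error rate.

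**The planned test does not lose much power.** A reader might take 67%, 56% and 38% as the power of the planned ANCOVA. They belong to a z-test with a corrected standard error. The planned ANCOVA would still reject about 76%, 74% and 69% of the time at a difference of 0.7. Its main fault is false positives, so those rejection rates are not power at a 5% level.

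**Conclusion.** The point holds in conditional form. The arithmetic of 78, 87 and 174 is correct for independent patients, but assignment is by clinic with two clinics per arm, so the stated 80% and 5% require zero between-clinic variance.

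For ICCs of 0.01 to 0.05, the ANCOVA as described has a true type I error of about 9.5% to 25%. A valid clinic-level test has power of about 28% to 17%. These sizes rest on the assumed ICC range and the even split. The reproduction of 78 with a design effect of 1, and the 2 degrees of freedom, do not depend on the ICC.

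A clinic-aware analysis would correct the variance. It would not remove confounding from the non-random choice of clinics, which the article already names as a limitation.

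**What to change.** 1. **Sample size determination.** State that 80% power assumes independent patients and an ICC of 0. Give the power over a stated ICC range for the analysis that will actually be primary. For the analysis in item 2, under the assumptions above, that is about 35%, 28%, 24% and 17% at ICC 0, 0.01, 0.02 and 0.05.
2. **Data analysis.** Name one clinic-aware primary analysis: baseline-adjusted clinic means compared between arms on 2 degrees of freedom. Report the results of all four clinics. Keep the patient-level ANCOVA as a secondary analysis, described as conditional on these four clinics.

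A mixed model with a random clinic intercept is not an interchangeable alternative here. With four clinics, its clinic variance would be estimated as zero in about 51%, 43% and 28% of trials at ICC 0.01, 0.02 and 0.05. Inference can then fall back to patient level. In a check that assumed residual degrees of freedom in those trials, the overall type I error was about 5% to 7%. That is a modest excess, but it is a reason to fix one method in advance.

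The change needs only rewording and no new patients. The price is a much lower stated power and a wider interval. Even at ICC 0, the 95% half-width would be around 4.303 × 0.2496 = 1.07 percentage points, against 1.96 × 0.2496 = 0.49 for the patient-level analysis.
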